### Outcome assessment test indicators

After the subjects agreed to participate in the intervention, a preliminary assessment was made. Tests were performed before the intervention (baseline), 4 weeks later (mid-term), and 6 weeks (end of intervention). The tested variables include (1) dynamic balance, (2) static balance, and (3) flexibility.

### Primary outcome

#### Dynamic balance

Dynamic balance is evaluated using the Star Excursion Balance Test (SEBT) [40]. SEBT is a comprehensive quality including strength, flexibility, and coordination. In the test, the subject is required to stand on one foot, maintain physical balance and use the affected leg as the support. The non-supporting leg faces the front of the supporting leg. Extend as far as possible in the posterior-inward direction and posterior-outward direction, retract and close the supporting leg, and then start the next extension. During the test, if the subject’s supporting leg moved or the non-supported leg touched the ground, it was considered failure. The farthest point of the unsupported leg from the starting point to the extension direction is the farthest distance (cm) reached by the subject, which is also the target data for all tests in this study. Before the formal test, the subjects performed 4 test exercises. The subjects measured 3 times in each direction and rested for 20 s between each time. The average of the 3 test data was the subject’s final test score. SEBT has been proven to be an effective method for evaluating ankle stability [41], and it has good internal reliability (ICC = 0.86–0.94) and retest reliability (ICC = 0.89–0.93) [42].

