### Sample size calculation

The sample size is calculated by the software G*Power 3.1.9 for Windows (G*Power© from University of Dusseldorf, Germany) [31]. The calculation of the sample size is regarded as the calculation of power, and its purpose is to observe whether there is a significant difference in the outcome indicators. This study consists of 3 groups and 3 measurements, the statistical power (1-β err prob) is 0.8, the type I error probability (α) is 0.05, the statistical analysis method is mixed-type analysis of variance, and the amount of effect obtained in the preliminary trial is 0.25, which is calculated by the software The sample size is 54 participants in total, with 18 participants in each group. At the same time, considering the 20% dropout rate and the equivalence between the groups, the sample size is 66 participants, and each group has 22 participants.

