### Statistical analysis

Statistical analysis was performed through the statistical package for social sciences software (The Statistical Package for Social Sciences, SPSS 23, SPSS Inc., Chicago, IL, USA). The normal distribution of variables is carried out by Shapiro-Wilk. Descriptive statistical analysis is described in the form of mean ± standard deviation. Through mixed two-factor multivariate analysis of variance, the effects of intervention groups (such as TC + KT, KTp + TC, KT) and time (such as before, during, and after intervention) were analyzed by reasoning. Multiple comparisons were made through post hoc analysis and Bonferroni correction for the variables of the variance analysis significance results. According to Cohen’s method, the effective amount is calculated. This method divides the effect amount into large (0.8), medium (0.50–0.79), and small (0.20–0.49) [45]. The alpha level for all tests is set to 0.05. A single-factor multivariate analysis of variance was used to compare the subjects’ baseline age, height, weight, and leg length data to explore whether the groups are homogeneous.

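### SEBT reach is analysed in raw centimetres with no leg-length adjustment, which costs some precision in between-group comparisons but not in the group-by-time test

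*Protocol article*

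**What the plan says.** Under Primary outcome, Dynamic balance, the SEBT measure is the farthest point touched by the free leg. This "is the farthest distance (cm) reached by the subject, which is also the target data for all tests in this study". Each direction is tried three times: "The average of the 3 test data was the subject’s final test score". Neither division by leg length nor any other scaling is stated.

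Under Statistical analysis, leg length appears once, in a one-factor multivariate comparison of "baseline age, height, weight, and leg length data to explore whether the groups are homogeneous". The outcome analysis is described as follows: "Through mixed two-factor multivariate analysis of variance, the effects of intervention groups" and of time are examined. It continues: "Multiple comparisons were made through post hoc analysis and Bonferroni correction", for variables with a significant result. Effect sizes follow Cohen's bands. No covariate is named. The article does not say whether the post hoc contrasts compare groups at a visit or visits within a group, nor which SD scales the effect size.

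**The concern.** The task is to stand on one leg and extend the other as far as possible, so reach in cm reflects limb length as well as dynamic balance. Limb length is a nuisance here. A baseline homogeneity test does not remove it from the outcome, and with about 18 to 22 players per group a non-significant test still allows an appreciable difference.

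What is at stake is precision. Between-player leg length widens the SD behind the group effect, behind group contrasts at one visit, and behind a Cohen's d that uses that SD. A chance difference in leg length between groups also shifts those contrasts. The value needed to remove this is already collected.

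**Working it through.** **Inputs from the article.** "This study consists of 3 groups and 3 measurements"; "the statistical power (1-β err prob) is 0.8"; "the type I error probability (α) is 0.05"; pilot effect 0.25, read here as Cohen's f (its outcome is not named); 54 players before dropout, 18 per group; SEBT retest ICC 0.89-0.93.

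**Not in the article, so assumed.** The SD of reach, its relation to leg length, and the correlation ρ between visits. I use ρ = 0.5, and ρ = 0.89 with the lower retest ICC as a proxy.

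**The stated sample size.** With k = 3 groups and m = 3 visits, the interaction test has λ = f²·N·m/(1−ρ). It gives N = 54 at ρ = 0.2 (power 0.805) and N = 36 at ρ = 0.5. As neither ρ nor the tested effect is stated, 54 cannot be confirmed. It serves below only as a fixed N.

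**Step 1: possible share of variance.** If reach = leg length × normalised reach, with independent factors, then to first order share = CV_L²/(CV_L² + CV_R²).
- CVs 4% and 10%: 16/116 = 14%
- CVs 5% and 8%: 25/89 = 28%
- CVs 6% and 6%: 36/72 = 50%

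**Step 2: effect on each test.** Let leg length explain a share R² of single-visit variance and add a constant to each player's reach. Removing it gives f_adj = f/√(1−R²) and ρ_adj = (ρ−R²)/(1−R²).

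Group-by-time at ρ = 0.5, R² = 0.25:
- before: λ = 0.0625 × 54 × 3/0.5 = 20.25
- after: λ = (0.0625/0.75) × 54 × 3/(1 − 0.333) = 20.25, unchanged

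Group effect, λ = f²·N·m/(1 + (m−1)ρ):
- before: 0.0625 × 54 × 3/2 = 5.06
- after: 0.0833 × 54 × 3/1.667 = 8.10

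Power at N = 54:

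| R² | Group, ρ=0.5 | Group, ρ=0.89 | Group×time, ρ=0.5 | Single-visit variance ratio |
|---|---|---|---|---|
| 0 | 0.484 | 0.363 | 0.958 | 1.00 |
| 0.10 | 0.554 | 0.402 | 0.958 | 0.90 |
| 0.25 | 0.696 | 0.478 | 0.958 | 0.75 |
| 0.40 | 0.881 | 0.587 | 0.958 | 0.60 |

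**Step 3: Cohen's d.** If d is scaled by the between-player SD, raw-cm d is √(1−share) times the normalised d: 0.93, 0.85 or 0.71 for shares of 14%, 28% and 50%. A d of 0.50 then reads as 0.46, 0.42 or 0.35.

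**Step 4: ratio against covariate.** Illustrative simulation: 18 per group, leg length 90 ± 5 cm, stable SD 4 cm, visit noise 3 cm, largest gain 3 cm.
- Reach rises 0.9 cm per cm of leg: interaction power 0.363 raw and 0.363 as a ratio; group effect 0.089 raw, 0.139 as a ratio.
- Reach rises 0.5 cm per cm: group effect 0.114 raw, 0.119 as a ratio.
- Reach unrelated to leg length: group effect 0.170 raw, 0.089 as a ratio.

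**Step 5: if baseline SEBT is already adjusted for.** At ρ = 0.89 and R² = 0.25, residual variance without leg length is 1 − 0.89² = 0.2079. With it, ρ_adj = 0.64/0.75 = 0.853, and the residual is 0.75 × (1 − 0.853²) = 0.204. The ratio is 0.98, a gain of about 2%.

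**The case against.** The strongest reply is that each player is measured at baseline, 4 and 6 weeks, and the group-by-time term, which best isolates a treatment effect, gains nothing. This stands. A reader might infer that raw centimetres weaken or bias the primary comparison as a whole. The documents do not support that: allocation is randomised, a constant leg-length contribution cancels in within-player change, and a chance imbalance would already show in baseline SEBT.

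It can also be said that the group main effect averages in the pre-treatment visit and is a poor treatment contrast in any unit, and that the SD behind Cohen's d is not stated. Both are fair. Even so, the Statistical analysis section names group and time effects without naming the interaction, and adds post hoc comparisons and effect sizes. The quantities that carry the extra variance are therefore within what the plan may report.

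The 14-50% range rests wholly on assumed CVs and strict proportionality, and its upper end needs the two CVs to be equal. It describes between-player variance at one visit and says nothing about the interaction's error term. Finally, raw cm with repeated measures is internally coherent, and no passage contradicts it.

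**Conclusion.** The point holds in a limited form. The article fixes raw cm as the SEBT measure and uses leg length only to check baseline comparability. This leaves avoidable variance in the group effect, in group contrasts at one visit, and in a Cohen's d scaled by between-player SD. It adds no systematic bias and does not affect the group-by-time test, provided the leg-length contribution is stable over the six weeks.

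The size cannot be derived from the document. The figures above are conditional on an assumed share, an assumed correlation, and 0.25 read as Cohen's f. If the comparisons adjust for baseline SEBT, which the article does not state, little remains to be gained. This is a minor, optional improvement.

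**What to change.** Before analysis, state for each SEBT direction that between-group comparisons include baseline leg length (mean-centred) as a covariate, or that reach is analysed as a percentage of leg length. Report raw cm as well in either case. No new composite over directions is needed.

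The covariate form is safer, because the ratio can lose precision when reach is not close to proportional to leg length. It costs one error degree of freedom for the group effect (54 − 3 = 51 becomes 50). If baseline SEBT is adjusted for instead, leg length may be left out with little loss.

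No new data are needed, but the change is not free: it alters the analysis of a primary outcome. By the dates under Trial status, recruitment was to end on 30 October 2021 and procedures by the end of December 2021, while the article appeared in February 2022. The change may therefore come after data collection. It should be dated, made without sight of results by group, and declared as an amendment. The ratio form would also change the outcome scale, and the article does not say on which outcome the pilot effect of 0.25 was obtained.

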#### Static balance

Static balance is assessed by the UniPedal Stance Test (UST) with closed eyes. The subjects were asked to stand barefoot, eyes closed, arms crossed on the chest, legs close together, and toes forward. When the subject heard the start command, the subject closed their eyes and chose the affected foot as the supporting leg to stand, and the other leg was bent and raised to the height of the knee joint of the supporting leg until the subject lost balance. Calculate the effective time for the subject to stand on one leg with a stopwatch, and start timing when the start command is issued. The time will stop when one of the following situations occurs: (1) arms are not crossed over the chest, (2) use a non-supporting leg to touch the ground or stay away from the supporting leg, (3) the supporting leg is displaced, (4) eyes are opened, and (5) the standing time has reached 45 s. Each subject performed 3 repetitive tests with a 20-s break between each test. The average of the 3 tests was used as the subject’s final test score and used for statistical analysis. The closed-eye single-foot test has been proved by related studies to have high score reliability (ICC = 0.998) [43].

### Secondary outcome

#### Flexibility

Flexibility is evaluated by the Toe Touch Test (TTT). The subject stood on the wooden box with his feet aligned, toes facing forward, straight legs bent at the hips, and tried his best to touch the toes with his hands. The knee joints could not bend while the body was bent down. Subjects are required to do their best to complete the test without bending or pain in the knee joint during the test. The value of the ruler touched by the hand is the distance (cm) reached by the subject. Each subject performed 3 repetitive tests with a 20-s break between each test. The average of the 3 tests was used as the subject’s final test score and used for statistical analysis. The standing flexion test has been proven to have good test-retest reliability (ICC = 0.89) [44].

### Safety measurements

Any unexpected adverse events that occurred during the 6-week intervention period will be reported to the research assistant, and the causal relationship between Tai Chi exercises and Kinesio taping effects will be evaluated. If a serious sports injury or other adverse event occurs, the research assistant will immediately report to the project leader and the Sports Science Ethics Committee of Beijing Sport University; they will decide whether the participant need to withdraw from the study.

### Data collection

The demographic information of the subjects will be collected during the recruitment process. The data of the primary and secondary results will be collected by specialized result assessors at baseline, 4 weeks of intervention, and 6 weeks of intervention. All result assessors conduct standardized training on test methods before intervention to ensure that all subjects have equal test conditions.

In order to ensure the attendance rate of the participants and provide more complete data results, we will provide all participants with free Tai Chi champion teaching services and a reward of 100 yuan. It will be distributed through WeChat after 6 weeks of intervention.

### Data management

The main and secondary results of the test will be recorded through the case report form (p-CRF), and the paper version of the data will be processed electronically through the free data management software EpiData Manager promptly on time. Two result evaluators separately reviewed and confirmed the data and converted it into a format that can be used for statistical analysis.

### Statistical analysis

Statistical analysis was performed through the statistical package for social sciences software (The Statistical Package for Social Sciences, SPSS 23, SPSS Inc., Chicago, IL, USA). The normal distribution of variables is carried out by Shapiro-Wilk. Descriptive statistical analysis is described in the form of mean ± standard deviation. Through mixed two-factor multivariate analysis of variance, the effects of intervention groups (such as TC + KT, KTp + TC, KT) and time (such as before, during, and after intervention) were analyzed by reasoning. Multiple comparisons were made through post hoc analysis and Bonferroni correction for the variables of the variance analysis significance results. According to Cohen’s method, the effective amount is calculated. This method divides the effect amount into large (0.8), medium (0.50–0.79), and small (0.20–0.49) [45]. The alpha level for all tests is set to 0.05. A single-factor multivariate analysis of variance was used to compare the subjects’ baseline age, height, weight, and leg length data to explore whether the groups are homogeneous.

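### Baseline enters the planned mixed (M)ANOVA as a level of time and not as a covariate: valid with complete data, but less precise than a baseline-adjusted mixed model

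*Protocol article*

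**What the plan says.** The Statistical analysis section of the protocol article gives one inferential model: "Through mixed two-factor multivariate analysis of variance, the effects of intervention groups" and, after listing the arms, "time (such as before, during, and after intervention) were analyzed by reasoning". The visits are baseline, week 4 and week 6 (Outcome assessment test indicators), and the Sample size calculation section confirms that "This study consists of 3 groups and 3 measurements". The pre-intervention visit is therefore one of three levels of the repeated factor.

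The software is given as "The Statistical Package for Social Sciences, SPSS 23, SPSS Inc., Chicago, IL, USA"; no procedure within it is named. Significant results lead to Bonferroni-corrected post hoc comparisons, without saying whether arms are compared on visit means or on changes.

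The baseline outcome is not listed as a covariate. A separate one-way multivariate test is to "compare the subjects’ baseline age, height, weight, and leg length data to explore whether the groups are homogeneous".

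On losses, the sample size section says "considering the 20% dropout rate and the equivalence between the groups, the sample size is 66 participants".

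**The concern.** In a randomised trial no treatment effect can exist before treatment starts. Making that visit a response level has two consequences. The group main effect averages a visit with no effect together with two visits that may have one. The group-by-time term works through differences from baseline, and so carries the full measurement and biological noise of the baseline value. Using baseline as a covariate removes only the part of it that predicts follow-up, which is the more precise use of the same data.

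A second, smaller issue is missing visits. The usual repeated-measures ANOVA procedure in SPSS analyses only players with every visit. The contrasts then rest on the assumption that completers represent all randomised players. There are reasons why losses might relate to treatment: players who develop a skin allergy to the tape are removed (Placebo Kinesio taping section), and the Discussion foresees difficulty keeping to the Tai Chi programme.

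At stake are precision in a trial of 22 players per arm, and the assumption needed to handle dropout.

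**Working it through.** **Inputs.** From the protocol article: three arms at 1:1:1, 22 per arm, three visits, 20% dropout (Study design; Sample size calculation). Assumed: equal variance σ² at each visit and a common correlation ρ between visits. The protocol gives no ρ, so the range is 0.2 to 0.9. The nearest figure is the SEBT retest ICC of 0.89–0.93 (Dynamic balance), a reliability that may overstate the correlation over six weeks.

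**The plan's own figures.** 54 × 1.2 = 64.8, rounded up to equal arms of 22, gives 66. The 54 itself cannot be reproduced from what is stated, because ρ and the effect tested are missing. For an interaction test with f = 0.25, power 0.80, α 0.05 and sphericity, 54 results at ρ of about 0.20 to 0.22; at ρ = 0.5 the same test needs 36. This does not show 54 to be wrong, and it does not establish ρ.

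**Group main effect.** If the effect is δ at weeks 4 and 6 and 0 at baseline, the average over visits is (0 + δ + δ)/3 = 2δ/3.

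**Precision of a two-arm contrast at week 6, no dropout.** Per-player variance is 2σ²(1−ρ) for change from baseline and σ²(1−ρ²) with baseline adjustment. The ratio is (1−ρ²)/[2(1−ρ)] = (1+ρ)/2.

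**With 20% dropout.** 66 × 0.20 = 13.2 players are lost, leaving 52.8. Assume half of the loss falls before week 4 and half after. The complete-case change contrast was compared with a mixed model that keeps baseline in the outcome vector with a common mean across arms. The last column shows the power of that model where the planned contrast has 80%.

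| ρ (assumed) | Variance ratio, no dropout | Variance ratio, 20% dropout | Power in place of 80% |
|---|---|---|---|
| 0.2 | 0.60 | 0.60 | 95% |
| 0.5 | 0.75 | 0.74 | 90% |
| 0.7 | 0.85 | 0.83 | 87% |
| 0.9 | 0.95 | 0.93 | 83% |

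**Source of the gain.** Keeping incomplete players while leaving baseline as a time level lowers the standard error only from 0.426 to 0.409 at ρ = 0.2, from 0.337 to 0.327 at 0.5, and from 0.151 to 0.148 at 0.9 (in units of σ), that is by about 2% to 4%. Nearly all of the gain comes from baseline adjustment.

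**The case against.** **The planned test is legitimate.** A reader might infer that the planned analysis is wrong. It is not: with complete data the group-by-time test is valid, and its 4 degrees of freedom are simply (3−1)(3−1). The two-thirds dilution matters only if the group main effect is used for inference, and the protocol does not say which term decides.

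**Baseline SEBT and UST are not ignored.** The homogeneity test covers only "baseline age, height, weight, and leg length data to explore whether the groups are homogeneous", which might suggest that baseline balance is never examined on the outcomes. But those values are in the model as a time level, and contrasts with that level subtract baseline differences. The homogeneity test is described as exploratory, not as a correction.

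**The gain may be small.** At ρ of 0.89–0.93 the variance factor is 0.945–0.965, a reduction of about 2–3% in standard error. This stands if arms are compared on change. If the unspecified post hoc comparisons use raw week-6 means, the factor is 1−ρ²: 0.96, 0.75, 0.51 and 0.19 at ρ 0.2, 0.5, 0.7 and 0.9, so that a high correlation favours adjustment. Under neither comparison does adjustment lose more than about one degree of freedom.

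**Deletion of incomplete players is inferred.** The protocol names SPSS 23 but no procedure, and SPSS 23 also fits mixed models. A missing-data rule may stand in a fuller document. The sample size already allows for 20% loss. So the loss of about 13 players is conditional. The Abstract's arm sizes (20 + 17 + 16 = 53) are close to 52.8, and a reader might take them as completers with uneven loss. The text calls them randomised, so they cannot support that.

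**The remedy does not rescue everyone.** With baseline as a covariate, a player with no follow-up adds nothing. If half of the dropout falls before week 4, about 6.6 of the 13.2 are regained. The claim that every randomised player is used fits only the version that keeps baseline in the outcome vector with a common mean.

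**Week 6 is a choice.** The protocol does not name a decisive visit. Reading the effect at the end of intervention is reasonable, but should be stated as a decision.

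**Conclusion.** The point holds as a worthwhile improvement, not as an error that invalidates the plan. The stated model puts baseline on the response side, which gives away precision. The variance could be multiplied by 0.60 to 0.95 for ρ from 0.2 to 0.9, with little to gain near 0.9 if arms are compared on change. These figures assume equal variances, a common correlation and, for the dropout results, the loss pattern stated above. Keeping players with incomplete visits adds little precision. Its value is that it replaces reliance on complete cases with the weaker missing-at-random assumption. That matters only if the SPSS procedure used would delete those players, which is likely from the ANOVA wording but not stated.

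**What to change.** Replace the model sentence in Statistical analysis. For each outcome, fit a linear mixed model to weeks 4 and 6 with arm, time, arm-by-time and the baseline value of that outcome, and an unstructured covariance. Include every player with at least one follow-up visit, in the allocated arm. To include all randomised players, keep baseline in the outcome vector with a common mean across arms. Report the week-6 arm contrasts with 95% confidence intervals, and keep the planned Bonferroni correction across the pairwise contrasts. Describe baseline characteristics without significance tests.

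No new data are needed, and SPSS 23 fits the model. The cost is about one degree of freedom, and the sample-size basis, a mixed ANOVA, becomes approximate and should be described so. The Trial status section expects completion by the end of December 2021. The change should therefore be dated and recorded as made before outcome data are analysed; if analysis has begun, it should be reported as a departure from the plan.

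### SEBT and UST are both primary, every test is at 0.05 and no control across them is stated; if they are tested separately, the chance of a false positive primary result is about 9 to 18.5%, not 5%

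*Protocol article*

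**What the plan says.** All references are to the protocol article.

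- **Two primary instruments.** The Primary outcome heading covers Dynamic balance (SEBT) and Static balance: "Static balance is assessed by the UniPedal Stance Test (UST) with closed eyes". The Toe Touch Test (TTT) is the first item under Secondary outcome.
- **SEBT is scored by direction.** "The subjects measured 3 times in each direction and rested for 20 s between each time". The averaging described is over the three repeats. No average over directions is defined. The sentence on reaching names two posterior directions, and the sentence before it mentions the front, so two or three directions can be read from it.
- **Three measurement times.** These are baseline, week 4 and week 6. None is called primary.
- **Error rate.** Statistical analysis says "The alpha level for all tests is set to 0.05". The model is a multivariate analysis of variance with group and time as its two factors. On correction it says: "Multiple comparisons were made through post hoc analysis and Bonferroni correction for the variables of the variance analysis significance results".
- **Sample size.** The calculation for the mixed model uses a single alpha of 0.05 and a single effect, and it does not name the outcome to which that effect belongs: "the amount of effect obtained in the preliminary trial is 0.25".

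**The concern.** A trial with several primary variables needs either one that decides or a rule that shares the error among them. Here the stated rule is 0.05 everywhere. The stated correction starts only after a variable has already passed at 0.05, so it limits error among the comparisons within that variable and not the number of variables that get a chance.

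The trial could therefore report success on UST, on an SEBT average built later, or on any single direction. The headline result could be picked after the data are seen, and 0.05 would not be the error rate of the primary claim. The sample size section does not settle the matter, because its effect of 0.25 is not attached to any outcome.

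**Working it through.** **1. The plan's own figure.** The article states no error rate across the primary variables, so there is none to reproduce. Its only related figure is N = 54. For a group-by-time effect with f = 0.25, three groups and m = 3 measurements, the noncentrality is λ = f²·N·m/(1−ρ), with 4 and 2(N−3) degrees of freedom. The correlation over time, ρ, is not given.

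- ρ = 0.2: λ = 0.0625 × 54 × 3/0.8 = 12.66, power 0.805. This reproduces 54.
- ρ = 0.5: 36 participants are enough for 80% power.
- ρ = 0: 69 are needed.

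So 54 fits one primary group-by-time test at 0.05 with ρ near 0.2. It makes no allowance for several primary tests.

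**2. Number of primary variables.** There are two if SEBT gives one score, three with two directions plus UST, and four with three directions plus UST.

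**3. Independent tests.** The chance of at least one false positive is 1 − 0.95^k.

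- k = 2: 9.75%
- k = 3: 14.3%
- k = 4: 18.5%

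**4. Correlated variables.** The article gives no correlations, so these are assumed. The simulation had every variable null, 18 per group, three times, correlation 0.5 over time, a separate group-by-time F test per variable, and 40,000 trials per row.

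| Correlation among directions / with UST | Two variables | Three | Four |
|---|---|---|---|
| 0 / 0 | 9.7% | 14.6% | 18.5% |
| 0.5 / 0.2 | 9.6% | 13.8% | 17.2% |
| 0.7 / 0.3 | 9.6% | 12.9% | 15.5% |
| 0.8 / 0.5 | 9.2% | 11.6% | 13.9% |
| 0.8 / 0.8 | 7.9% | 10.3% | 12.2% |

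With two variables only the correlation with UST matters. Simulation error is about 0.4 percentage points, so 14.6% agrees with the exact 14.3%. The last row is an extreme case, since it makes a timed eyes-closed stance as close to a reach distance as two reach directions are to each other.

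**5. If a multivariate test came first.** A single Wilks test of group by time over all the variables rejects in 5% of trials when all are null. Per-variable tests run only after it passes then give 2.5 to 4.5%, so in that case the gate works.

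Next, give UST alone a real effect: one group shifted by 1.5 SD at week 6 and by 0.7 of that at week 4 (assumed), with correlations from 0/0 to 0.8/0.3. The chance of at least one false SEBT direction behind the gate is then 10 to 14% with three directions and 8 to 10% with two. With a shift of 1.0 SD it is 8 to 11% and 7 to 8%. Only with a single SEBT score does the gate hold at 5%, because two variables behind a joint test form a closed procedure.

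**The case against.** **The model is multivariate.** The separate tests behind the 9 to 18.5% are not spelled out in the article, and a multivariate gate would hold the error at or below 5% when every variable is null. This stands, and it makes the figures conditional. But no gate is stated, the sample size section refers only to a mixed analysis of variance, and with SEBT scored by direction a gate fails once one variable truly responds (step 5).

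**Two post-baseline times.** A reader might infer that four variables at weeks 4 and 6 make eight tests at 0.05, or that the error is simply three times the stated level. The documents do not support either. Time is a factor within one model, and comparisons at single times fall to the post hoc step, where Bonferroni is stated. Eight independent tests would give 1 − 0.95^8 = 33.7%, but that analysis is not planned. A factor of about three needs four separately tested variables and assumed correlations.

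**Three directions.** The count is not stated, and two is an equally literal reading. This is why a range is given.

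**A condensed article.** A testing order may sit in a fuller document. That would excuse silence. The article does, however, state an alpha for all tests and the scope of Bonferroni, and naming the primary variable belongs in the protocol.

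**The remedy.** A composite with a fixed sequence is one valid scheme among several. A move to a week-6-only test would cost power (see the fix). Both points are accepted.

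**Conclusion.** The point holds in conditional form. Two instruments are primary, one of them scored by direction. No primary variable or time point is named, and no error control across the primary variables is stated.

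If the variables are tested separately by the group-by-time effect, the chance of at least one false positive primary result is about 9 to 10% (two variables), 12 to 14% (three) or 14 to 18.5% (four). This assumes 18 per group, correlations of 0 to 0.8 among directions and 0 to 0.5 with UST. If every correlation were 0.8 the figures would be about 8%, 10% and 12%, still above 5%.

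An explicit multivariate gate would bring the error to 5% or below only when every variable is null, unless SEBT is first reduced to one score. The change is worth making because it is cheap and fixes in advance which result carries the trial.

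**What to change.** Amend Primary outcome and Statistical analysis as follows.

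1. Name one primary variable, the SEBT composite (mean of the measured directions), and list the directions.
2. Test it by the planned group-by-time effect at 0.05. Make the arm contrasts at week 6 the key comparisons, Bonferroni-corrected as already stated.
3. Test UST in the same way, only if SEBT is significant. Alternatively, use Holm across SEBT and UST.
4. Make single directions, week-4 contrasts and TTT secondary.

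**Cost.** This takes a few lines of wording and no new data. Under the fixed sequence, UST alone can no longer carry the trial. Under Holm, the smaller p-value is tested at 0.025. At N = 54 and f = 0.25, power for that step falls from 0.96 to 0.92 if ρ = 0.5, from 0.805 to 0.72 if ρ = 0.2, and from 0.70 to 0.59 if ρ = 0.

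**What to avoid.** Do not replace the mixed model with an unadjusted week-6 comparison. With f = 0.25 and N = 54, λ = 0.0625 × 54 = 3.375 on 2 and 51 degrees of freedom, and power is only about 0.34. Adjusting for baseline at an assumed correlation of 0.7 gives λ = 3.375/(1 − 0.49) = 6.62 and power 0.60.

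**Timing.** Trial status expected procedures to end in December 2021, before the article appeared. The change should therefore be dated and its position relative to the analysis stated. If results have already been seen, the order must be reported as set afterwards.
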